## Abstract

**Methods::**

A randomized, double-blind, placebo-controlled parallel trial will be conducted to assess 20 patients with chronic upper body pruritus for 3 months who have been diagnosed with allergic atopic dermatitis or seborrheic dermatitis. The patients will be randomly allocated to either the placebo-control (n = 10) or treatment (n = 10) group. The total study period will be 8 weeks (i.e., administration of *Sopoongsan* or placebo drugs for 4 wk and follow-up for 4 wk). Participants will be allowed to receive external treatment, except for antipruritic medications administered orally, throughout the study period. The primary outcome measure will be the numeric rating scale results for itching, whereas the secondary outcome measures will be questionnaire survey (Dermatological Life Quality Index and Epworth Sleepiness Scale) findings and the immune response index, including interferon gamma, interleukin-4, immunoglobulin E, thymic stromal lymphopoietic protein, and histamine, to investigate the biological mechanisms underlying chronic pruritus.

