The biological mechanisms underlying chronic pruritus are complex and multifactorial.^[1]^ The itch-sensitive neurons originating in the skin are stimulated by several pruritogens, including histamine, immune cells, keratinocytes, and nerves.^[4]^ Histamine activates neurons via the histamine receptor 1, leading to the opening of the heat- and capsaicin-gated transient receptor potential (TRP) channel. TRP channels are key transduction ion channels on the plasma membrane that exacerbate the excitation of neurons and promote itching. Moreover, other non-histaminergic endogenous pruritogens are released from keratinocytes, such as cytokine thymic stromal lymphopoietic protein (TSLP), which activates neurons via the TSLP receptor leading to the opening of TRP ankyrin 1 channels. Activating TRP leads to depolarization, action potential firing, and transmission of itch-neuronal signals from the periphery to the central nervous system.^[4]^ The itch signal is transmitted to areas of the brain that are involved in sensation, evaluative processes, emotion, reward, and memory.^[1]^ Collectively, the analysis of pruritus-related immune cytokines may help elucidate the therapeutic biological mechanisms by which *Sopoongsan* can benefit patients with chronic pruritus. Nonetheless, RCTs investigating the *Sopoongsan*-induced changes in the immune response in serum samples of patients with chronic pruritus are limited.

In this study, we report our study design and plans for evaluating the effectiveness of *Sopoongsan* in patients with chronic pruritus and the feasibility for analyzing data collected during the whole process of the trial. Furthermore, we will elucidate the mechanism underlying the effectiveness of *Sopoongsan* in patients with chronic pruritus by measuring the levels of immune-related cytokines. The specific objectives of the study include the verification of research feasibility to assess the effectiveness of *Sopoongsan* for improving skin itching in patients with chronic upper body pruritus and the investigation of the possibility of immune indicators as therapeutic response biomarkers in response to *Sopoongsan* for skin pruritus.

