### 2.3. Randomization and blinding

The allocation of eligible patients to the control or *Sopoongsan* treatment group at a 1:1 ratio will be performed by an independent statistician using computer-generated block randomization. Each participant will be selected via systematic sampling and receive an identification code enclosed in an opaque envelope. This will be a double-blind study because the participants, researchers, and assessors collecting the data will be blinded to group assignment. If the blinding was disrupted such as in a medical emergency, the principal investigator will hold a researchers’ meeting to decide if unblinding is required. In this case, the unblinding will be informed to the institutional review board (IRB) within 24 h. The enrollment of participants, allocation sequence, and assignment of participants will be the responsibility of the Clinical Trial Center at the Kyung Hee Korean Medical Hospital, Kyung Hee University.

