##### 2.5.2.3. Molecular analysis.

Investigating changes in serum cytokine levels may help us understand the mechanism of action of *Sopoongsan* in patients with chronic pruritus. The serum levels of pruritus-related cytokines such as IFN-γ, IL-4, immunoglobulin E (IgE), and TSLP will be analyzed.^3^ The assessment will be conducted at baseline (visit 0) and 4 weeks after treatment (visit 3) for both groups. Blood collected from patients in both groups will be immediately centrifuged at a temperature below 4°C. The obtained plasma and serum samples will be stored at a temperature below −80°C until further analysis. The samples will be analyzed by Global Clinical Central Laboratories (Republic of Korea).

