### 2.7. Statistical methods

#### 2.7.1. Sample size.

This study will be an exploratory clinical trial to determine the degree of symptomatic improvement that can be achieved with *Sopoongsan* treatment in patients with upper body chronic pruritus. However, statistical hypotheses and effect sizes for the estimation of the sample size cannot be established. Therefore, as a pilot study based on research feasibility, this study considers a total of 20 subjects, 10 per group.

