#### 2.7.2. Statistical analysis.

All statistical analyses will be conducted using SAS® version 9.4 (SAS Institute, Inc., Cary, NC). The *p*-values will be two-sided and set at 5% level of significance. A complete set analysis will be conducted to analyze the effectiveness of the intervention, and a per-protocol analysis will be additionally verified. Missing data will be analyzed using the last observation carried forward imputation method. For efficacy analysis, the mixed-effect model for repeated measures will be used, with each group and visit time as fixed factors and subjects as random factors. Student’s paired *t* test will be used to compare the factors before and after treatment. All adverse events (including severe adverse events) will be classified by group.

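### The immune markers' most natural named analysis is a before/after paired t test, which has no treatment contrast; make a baseline-adjusted between-arm comparison the inferential one

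*Protocol article*

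**What the plan says.** Section 2.7.2 of the protocol article sets p-values that "will be two-sided and set at 5% level of significance" and then names two analyses. For efficacy there is a mixed model for repeated measures with group and visit as fixed factors and subject as random. In addition, a Student's paired t "test will be used to compare the factors before and after treatment". The section does not define the factors, does not say whether the paired test is run in each arm or over both, and does not call it descriptive. Nor does it say which outcomes the mixed model covers.

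Table 2 and Section 2.5.2.3 schedule blood for immune analysis twice, at baseline and at week 4, in both groups. The markers are secondary outcomes. The Introduction also lists as a specific objective "the investigation of the possibility of immune indicators as therapeutic response biomarkers". On size, Section 2.7.1 states that "this study considers a total of 20 subjects, 10 per group", and that "statistical hypotheses and effect sizes for the estimation of the sample size cannot be established".

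**The concern.** A paired test asks whether a mean changed from before to after. In a placebo-controlled trial that is a different question from whether the drug changed it. Placebo response and the natural course of the dermatitis contribute to the change, and so does the external treatment that Section 2.4 allows in both groups. Run within each arm, the test invites a comparison of two p-values, which is not a test of the difference between arms. Run over both arms pooled, it contains no treatment comparison at all.

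The markers are the most exposed outcome, because exactly one before value and one after value is the layout for which a paired t test is made. The Conclusions expect to show cytokine changes that give insight into the mechanism, and the Discussion offers the pilot as a basis for larger trials. A before/after p-value could feed straight into both claims.

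**Working it through.** **Inputs.** Ten patients per arm (Section 2.7.1), 1:1 allocation (Section 2.3), two-sided 5% level (Section 2.7.2), and markers at baseline and week 4 (Section 2.5.2.3). The sample size rests on feasibility, so the plan has no power figure to reproduce. The documents give no effect size or SD. The common change dz, which is the mean change divided by the SD of the paired difference, is therefore an assumption and is shown over a range.

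**Step 1: paired test in one arm.** With n = 10 the statistic follows a noncentral t distribution with 9 degrees of freedom and noncentrality dz × √10. The probability of significance is p = P(|T| > t(0.975; 9)). For dz = 0.5 the noncentrality is 0.5 × 3.162 = 1.58 and p = 29.3%.

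**Step 2: the misleading pattern when the drug does nothing.** If both arms have the same dz, they are independent with the same p. Significance on Sopoongsan but not on placebo then has probability p(1 − p).

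| Common dz (assumed) | p in one arm | p(1 − p) |
|---|---|---|
| 0.3 | 13.6% | 11.8% |
| 0.5 | 29.3% | 20.7% |
| 0.7 | 50.6% | 25.0% |
| 0.8 | 61.6% | 23.6% |
| 1.0 | 80.3% | 15.8% |

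A simulation of 100,000 trials per setting gave 20.7%, 23.6% and 16.1% at dz = 0.5, 0.8 and 1.0.

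**Step 3: the between-arm benchmark.** In the same simulated trials, a two-sample t test on change rejected in 5.0% at each of these settings. By symmetry half of that, 2.5%, favours the drug. The size of the common change does not matter, because it cancels between arms.

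**Step 4: pooled version.** If the paired test were run on all 20 patients, it would be significant in 56.5%, 92.4% and 98.9% of trials at dz = 0.5, 0.8 and 1.0, with no drug effect.

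**Step 5: the mixed model with only its listed terms.** Write the mean as intercept + group effect + visit effect, with a random subject effect and complete data. The estimated group effect is then the arm difference averaged over the visits in the model. A marker has two visits. The expected baseline difference is 0 by randomisation, and call the week-4 difference D. The group term estimates (0 + D)/2 = D/2, which is 50% of the quantity of interest.

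**Step 6: what a between-arm comparison can detect.** With 10 per arm, a two-sample t test on change has exact power of 19%, 40% and 56% for standardised differences of 0.5, 0.8 and 1.0. It reaches 80% at about 1.33.

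**The case against.** The strongest reply is that the section does name a between-arm analysis, and labels it as the one for efficacy. The markers are secondary outcomes measured in both groups, so the mixed model may be meant to cover them, with the paired test as a supporting description. This stands in part. A reader might infer that the before/after conclusions rest on within-arm paired tests, or that the markers are analysed only that way. The text supports neither reading: it does not say within-arm and does not assign the markers.

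A second reply is that an article condenses the plan, so a group-by-visit term, the handling of baseline and an exploratory marker-itch analysis may stand in the full plan. That also stands. The half-size group term is therefore conditional on the model being fitted as listed, and an unlisted marker-itch analysis is not in itself a fault.

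Three further inferences are tempting but not supported. The abstract lists histamine and Section 2.5.2.3 does not, but that section introduces its markers as examples, so there is no contradiction. An error rate over all paired tests cannot be fixed, because the text gives neither their number nor whether they are run by arm. The documents give no marker distributions, so skewness can only be a condition.

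None of this gives the paired test a treatment contrast. It remains a named test under the 5% rule with no descriptive label.

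**Conclusion.** The concern holds in a limited form. Section 2.7.2 names a significance test that cannot attribute change to Sopoongsan, and the two-occasion immune markers are the outcome it fits best. With equal improvement in both arms, the pattern of significance on Sopoongsan alone has a probability of about 21% to 25% for an assumed common change of 0.5 to 0.8 SD (12% to 25% over 0.3 to 1.0 SD), against 2.5% for a between-arm test. These figures assume normally distributed changes, complete data on 10 patients per arm and a paired test run by arm.

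The named alternative does not settle the matter as written: with only group and visit in the model and baseline kept as a response, it reports half of the week-4 marker difference. This is a worthwhile correction in an exploratory pilot. It does not show that the trial's efficacy analysis as a whole is invalid.

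**What to change.** For each immune marker, state that the between-arm comparison is the inferential one: ANCOVA of the week-4 value on group and baseline, on the log scale if the data are skewed, with a 95% CI. Report before/after changes within each arm as descriptive estimates with CIs and without p-values. For the biomarker objective, add an exploratory regression of week-4 NRS change on marker change, adjusted for group.

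All of this uses samples and scores already scheduled. The cost is a few lines of code and the loss of the before/after p-values. It will not make 10 per arm a powerful comparison (Step 6), so the interval should carry the message.

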### 2.8. Data management and monitoring

Information required by the protocol will be collected by the clinical research coordinator by filling out the case report forms. Data coding will be conducted; two research assistants will independently enter the data into Excel sheets, and the results will be verified by cross-checking. All documents obtained from the clinical trial will be preserved in confidential archives at the Kyung Hee Korean Medicine Hospital for 3 years. No information will be released without the permission of the principal investigator. The regular monitoring for patient safety, investigating adverse events, and reviewing quality control of the data will be performed by an independent monitoring committee not related to this study.

### 2.9. Ethical considerations, informed consent, and study registration

The IRB at Kyung Hee University Korean Medicine Hospital approved the protocol version 1.3 (Jun, 16, 2022) of this clinical trial and accepted responsibility for supervising all aspects of the study (KOMCIRB 2022-05-006-002). All participants will be willing to participate in this clinical trial and submit a signed informed consent form. Before consent, all participants and their families will receive an explanation of the potential risks and benefits. The study protocol (version 1.3) was registered with the Clinical Research Information Service of the Republic of Korea (KCT0007537). In the case of significant protocol changes, the research coordinator will request supplementation of the IRB and trial registries.

## 3. Discussion

Pruritus is the most common symptom in dermatology and constitutes more than one-third of dermatological presentations.^[12]^ However, there is limited evidence regarding pharmacological treatment methods for chronic pruritus, and clinical studies investigating the effectiveness and mechanism of action of pharmacological treatments for chronic pruritus are scarce.^[1]^ Thus, the present study aims to investigate the clinical effectiveness of *Sopoongsan* as pharmacological therapy in patients with chronic upper body pruritus.

In the Republic of Korea, the efficacy of *Sopoongsan* is approved for “itching caused by rising wind” by the Ministry of Food and Drug Safety and is specified in Dong-uibogam. To reflect the concept of “rising wind,” we will limit the participants’ lesions to the upper body in patients with allergic atopic or seborrheic dermatitis in the present study. Lesions on the upper part of the human body (i.e., head, neck, and upper limbs) are often caused by wind-warmth and wind-heat because wind tends to move upwards. Therefore, in the present study, based on the indications for *Sopoongsan*, the area corresponding to “rising wind” was limited to the upper body. In addition, in Korean traditional medicine, it is thought that symptoms of dry skin in the upper body are more likely to develop as a result of blood deficiency. Blood deficiency is known as any pathological change characterized by the deficiency of blood, which fails to nourish organs, tissues, and meridians/channels. Blood deficiency induces a pattern/syndrome marked by dry, rough, itchy, shriveled skin with rhagades, withering and loss of hair, numbness of the body surface, contraction of hands and feet, lusterless complexion, pale nails, dizziness and blurred vision, pale tongue, and fine pulse. *Sopoongsan* from Dong-uibogam is widely used to treat dry lesions in the Republic of Korea.

Itching is a response to skin conditions that cause allergic reactions or inflammatory responses. Recently, the understanding of the neuroimmune axis has uncovered new targets for the treatment of chronic pruritus. The skin barrier is functionally divided into three types based on immune cells. Type 1 immunity involves responses mediated by adaptive cells, such as type 1 helper T (Th1) cells and cytotoxic T cells, characterized by the production of INF-γ, and tumor necrosis factor-alpha. The type 1 immune response provides protection against intracellular pathogens and tumor cells and can promote chronic inflammatory processes, such as autoimmune skin diseases and allergic contact dermatitis. Type 2 immunity is mediated by adaptive type 2 helper T (Th2) cells as well as innate immune cells, including basophils, mast cells, and eosinophils, producing the effector type 2 cytokines IL-4, IL-5, and IL-13, which promote allergic inflammation and IgE production. Upstream promoters of the type 2 inflammatory process include TSLP, which can be directly secreted by keratinocytes.^[3]^ The Th1/Th2 immune balance is closely related to various immunological diseases, including allergies. Many investigators have revealed that Th2 immunity is responsible for allergic immune responses and the subsequent pathogenesis of allergic inflammatory diseases. Chronic inflammatory skin diseases (i.e., atopic dermatitis) are known to increase the expression of Th2 cytokines (i.e., IL-4, IL-5, and IL-13) in peripheral blood.^[15]^ As such, Th1/Th2 immune balance can be a very important indicator for itching, and we aim to analyze the changes in cytokines associated with Th1/Th2 immune responses to investigate the mechanism of action of *Sopoongsan* on chronic itching.

The proposed study has the limitation of being a small pilot clinical trial. However, this study could be a basis for large-scale clinical studies in the future because no current evidence clarifies the effectiveness of *Sopoongsan* in the treatment of chronic pruritus and pruritus-related cytokines changes. Another limitation is that targeting patients with dermatological diseases (i.e., atopic dermatitis and seborrheic dermatitis) and chronic pruritus to investigate the effectiveness of *Sopoongsan* is not specifically determined. The efficacy of *Sopoongsan* is on “itching that the wind rises” rather than confining to a disease, which is why the area of the lesions is limited to the upper body. Based on the results of this study, further research is expected.

## 4. Conclusions

This study will be the first clinical trial on *Sopoongsan*, which is used in the Republic of Korea, and will investigate the clinical effectiveness of *Sopoongsan* for the symptoms of upper body pruritus and changes in the immune response in patients with allergic atopic or seborrheic dermatitis. We expect to demonstrate improvements in chronic pruritus, including the intensity of pruritus and patients’ quality of life, as well as changes in the levels of pruritus-related cytokines to obtain an insight into the mechanism underlying the effectiveness of *Sopoongsan* in chronic pruritus and help identify potential alternative therapies for chronic pruritus.
